### 2.7. Statistical Analysis Plan

This exploratory randomised crossover trial is designed to estimate the pattern and magnitude of intervention effects on upper extremity function in individuals with cSCI. While primarily exploratory, the design allows for formal testing of superiority if a sufficiently strong intervention effect is observed.

In total, the study will randomise 40 participants to one of two intervention sequences. The crossover design enables paired comparison of intervention effects. Hence, a sample size of 34 evaluable participants will allow detection of a minimal clinically important difference (MCID) of three points in the primary outcome GRASSP-QtG with a power of 80% and a significance level of 5% (two-sided), as long as the corresponding within-group standard deviation does not exceed six points (corresponding to a medium effect size). Based on the number of patients with cSCI in previous years [11] and accounting for a 15% attrition rate, the study aims for a recruitment duration of two and a half years after first patient in to reach the calculated sample size of 40 participants.

Descriptive statistics will summarise the baseline characteristics of the study participants. Even though the SCI population is characterised by a predominance of males (~70%) [27,28], the neurological and functional recovery profiles have been found to be comparable between genders [29]. Therefore, no gender-specific stratification is planned. However, gender balance will be ensured within the study team for data collection, analysis, and authorship.

The primary and secondary outcomes will be analysed as changes within each period using linear mixed models. A two-sided significance level of α = 0.05 will be used for superiority testing. The model will include the baseline value measured at the start of the study, TREATMENT as a categorical variable with two levels (RT and OT), and PERIOD as a categorical variable with two levels (first and second) to assess the differences in changes in GRASSP-QtG between timepoints (i.e., t_1_–t_0_ and t_2_–t_1_). In addition, subject- and stratum-specific random intercepts will account for within-subject and within-stratum correlation across timepoints. To assess potential carryover effects, a second model will additionally include the TREATMENT × PERIOD interaction and SEQUENCE as a categorical variable with two levels (RT-OT and OT-RT). No interim analyses are planned for the main outcomes.

The primary analysis of this trial will follow the intention to treat principle, including all subjects in the statistical analysis who are randomised and provide a baseline (t_0_) assessment. Additionally, per-protocol analyses of all endpoints will be conducted as exploratory analyses to evaluate the effect of unilateral RT intervention under ideal adherence conditions (>75%, i.e., at least 14 sessions per intervention). In general, participants who discontinue the intervention (e.g., fulfilling exclusion criteria, early discharge or complications) will be encouraged to participate in an unscheduled assessment at least for t_1_ (or a timepoint before the individual end of study) and to ideally provide an assessment at least for the primary endpoint. To account for partially missing outcome data, linear mixed models assuming data are missing at random will be applied. In case of entirely missing outcome data, multiple imputation will be performed. The potential impact of missing values will be discussed in the final report.

Data analysis will be performed using contemporary versions of the statistical software packages R (Version 4.5.1, R Foundation for Statistical Computing, Vienna, Austria) and RStudio (Version 2025.05, RStudio, PBC, Boston, MA, USA), or any newer stable version available at the time of data analysis.

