### 2.3. Study Procedure

The CTU informs the study team when a patient who has been newly admitted to the SPC fulfils the main eligibility criteria. Patients who express interest in participating in the study receive verbal and written information (Supplement S2) about the study’s purpose, procedures, and potential risks from a qualified study team member. Potential participants are given at least 24 h to decide whether to participate. Written informed consent is obtained from all participants prior to enrolment.

The participants will be enrolled between day 16 and day 81 post-injury. Following enrolment, inclusion and exclusion criteria are verified, and the descriptive data (see Outcomes) of the participants are collected. Moreover, the stratification parameters ISNCSCI-FDP and GRASSP-Delto are extracted from the medical records and used for stratified randomisation. Furthermore, the participants together with their therapists decide which upper extremity to include in the study.

The baseline assessment t_0_ takes place within one week before the intervention begins and starts no later than day 82 after the injury. The intermediate t_1_ and post assessment t_2_ take place within one week after completion of the preceding intervention block. In case t_2_ is completed before day 150 after injury, the follow-up assessment t_3_ is conducted approximately 30 days after t_2_, but before day 186 after injury. Otherwise, the follow-up assessment t_3_ is omitted, and t_2_ has to be completed before day 186 after injury in line with the timepoints from the EMSCI study [17]. In every assessment, the primary and secondary outcomes (see Outcomes) are assessed by a team of assessors, all specifically trained in the study assessments. Each assessment lasts approximately three hours.

One week after starting the baseline assessment t_0_ (or t_1_ respectively), the randomly assigned intervention block starts (see Study interventions). The experimental intervention RT is conducted by members of the Armeo specialist group, which is specifically trained to deliver RT using Armeo devices at the SPC. The control intervention OT is conducted by experienced occupational therapists from the SPC. During both blocks, parameters characterising the interventions (see Further outcomes) and therapy adherence are documented by the therapists and study team.

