Furthermore, time during primary rehabilitation is a strong determinant of motor recovery and may therefore influence observed improvements during the first compared to the second intervention period. By including PERIOD and the baseline measurement in the linear mixed model, we account for overall time-related recovery effects and thereby reduce confounding by the underlying recovery trajectory when estimating the treatment effect. However, potential carryover effects will be explicitly assessed and considered in the interpretation of the results.

Additionally, whereas only one arm will be randomised to one of the two sequences of intervention blocks, both arms continue with the clinical routine therapy. Although the clinical routine therapy could affect the study objectives, it would not be ethical to restrict the clinical routine therapy during primary rehabilitation after cSCI. However, the influence on the primary objective is reduced by the within-subject comparison due to the crossover design, provided that the concomitant therapy does not differ systematically between the blocks.

Finally, by having stratified randomisation in the crossover design, new hypotheses can be generated from exploratory subgroup analysis. With this, more information about possible individualisation of therapy schedules dependent on the patients’ predicted recovery profiles can be provided in the future.

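### As a main effect on change scores, the t0 baseline cancels from the complete-pair treatment estimate, so Section 3 wrongly credits it with adjusting for recovery trajectory

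*Protocol article*

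**What the plan says.** Section 2.7 sets out the outcome and the terms of the primary model:

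- Outcome: "The primary and secondary outcomes will be analysed as changes within each period using linear mixed models", that is d1 = t1 − t0 and d2 = t2 − t1.
- Fixed effects: "The model will include the baseline value measured at the start of the study, TREATMENT as a categorical variable", plus PERIOD. No product of baseline and PERIOD is listed.
- Random effects: "subject- and stratum-specific random intercepts will account for within-subject and within-stratum correlation across timepoints".
- For carryover, "a second model will additionally include the TREATMENT × PERIOD interaction and SEQUENCE as a categorical variable with two levels". This model has no product of baseline and PERIOD either.
- Analysis set: "including all subjects in the statistical analysis who are randomised and provide a baseline (t_0_) assessment". Partly missing outcomes are handled by the mixed model under missing at random.

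Section 3 then states what the primary model achieves: "By including PERIOD and the baseline measurement in the linear mixed model, we account for overall time-related recovery effects", and the authors say that they "thereby reduce confounding by the underlying recovery trajectory when estimating the treatment effect".

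**The concern.** Section 3 itself treats time in primary rehabilitation as a strong driver of motor recovery. Participants also differ in where they stand on the recovery curve. Section 2.3 says "The participants will be enrolled between day 16 and day 81 post-injury", with t0 starting by day 82 and the first block one week after t0. On paper, then, block 1 can begin anywhere from about day 23 to day 89. Randomisation is stratified because predicted recovery differs between people.

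PERIOD takes out the average slowing between blocks. How much a given person slows can still differ, and that difference is noise in d1 − d2, the quantity that carries the treatment comparison. A reader of Section 3 will believe that the baseline term deals with part of this. If it does not, the report will describe an adjustment that was not made, and information collected at t0 will go unused.

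**Working it through.** **1. The plan's own figure.** Inputs from Section 2.7: difference 3 points, SD 6, two-sided 5%, 34 evaluable. Reading 6 as the SD of the paired RT − OT difference, the noncentrality is 3√34/6 = 2.915. A paired t-test gives 80.8% power at 34 participants, and 80.7% with 32 df once a period term is fitted. At 15% attrition, 34/0.85 = 40. Both figures reproduce, and this point does not affect them.

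**2. Cancellation.** For participant i in period j, with baseline b, stratum intercept s and subject intercept u:

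d_ij = μ + β·b_i + π·[j = 2] + τ·RT_ij + s + u_i + e_ij

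The within-participant difference is

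d_i1 − d_i2 = −π + τ·(RT_i1 − RT_i2) + (e_i1 − e_i2)

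- The terms β·b_i, s and u_i have gone.
- In RT-OT the mean of d1 − d2 is −π + τ; in OT-RT it is −π − τ. Half the difference is τ.
- The sum d1 + d2 contains τ once in both sequences, so it tells us nothing about τ.

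Hence, with complete pairs, the treatment estimate is half the between-sequence difference in mean d1 − d2, whatever the baseline values are.

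**3. With the interaction.** Adding γ·b_i·[j = 2] gives d_i1 − d_i2 = −π − γ·b_i ± τ + error. Baseline is now a covariate for d1 − d2 and can act on the estimate.

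**4. Numerical check.** Assumed inputs: true effect 3, four strata, baseline slope 0.25 in period 1 and 0 in period 2; 200 trials per scenario.

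| | 34 complete pairs: empirical SD of estimate | 40 randomised, 15% without period 2: empirical SD |
|---|---|---|
| No baseline or stratum | 1.086 | 1.183 |
| Protocol model | 1.086 | 1.181 |
| Baseline × PERIOD added | 1.070 | 1.112 |
| Stratum × PERIOD also added | 1.124 | 1.169 |

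- Complete pairs: the protocol model and the model without baseline and stratum gave the same treatment estimate in all 200 trials. Baseline × PERIOD moved it by 0.23 points on average. In a separate single data set the estimate was 2.3249 with and without baseline, and 2.1521 with baseline × PERIOD.
- With 15% of second periods missing, the protocol model moved the estimate by 0.07 points on average (maximum 0.36).
- The mean complete-pair estimate was 3.031 under the protocol model and 3.029 with baseline × PERIOD, so neither shows bias.

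**5. What baseline × PERIOD costs or gains in power.** Let R² be the share of the within-sequence variance of d1 − d2 that baseline explains. The document gives no value, so a range is shown. The SD becomes 6√(1 − R²) and the df 34 − 3 = 31. Estimating one covariate that is imbalanced by chance inflates the variance by about 1 + 1/(34 − 4) = 1.033.

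| R² | Power without inflation | Power with inflation |
|---|---|---|
| 0 | 80.6% | 79.4% |
| 0.1 | 84.5% | 83.4% |
| 0.2 | 88.4% | 87.4% |
| 0.3 | 92.1% | 91.3% |

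The comparison is with 80.7% for the model as planned.

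**The case against.** The strongest reply is that Section 3 credits PERIOD and baseline jointly, and speaks of overall recovery effects. PERIOD does remove the average difference between blocks, so a reader who inferred that the whole claimed adjustment is empty would be wrong. This stands; only the baseline half of the sentence is idle.

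Further points on that side:

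- **The planned data will not all be complete pairs.** Attrition of 15% is expected and everyone with a t0 value is kept. One-period participants add between-participant information, so the baseline main effect does shift the estimate, though slightly, and it may help the missing-at-random assumption. Even with complete pairs the standard error can change (by up to 0.18 in a simulation where the subject variance was usually estimated at zero). It is therefore too strong to say that the term has no effect at all. This stands.
- **The stratum intercept.** A reader might extend the criticism to it, since it cancels in the same way. Section 2.7 gives it only a correlation purpose, so there is no trajectory claim to correct.
- **Bias.** The word confounding in Section 3 may suggest that RT versus OT is biased without adjustment. Sequence is randomised within recovery strata, so it is not. Chance imbalance is already reflected in the standard error.
- **Calendar spread.** Days 23 to 89 are extremes; Section 3 expects the first block to start around three months after injury. The actual spread may be narrower.

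What none of this rescues is the statement that including the baseline reduces confounding by the recovery trajectory.

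**Conclusion.** The point holds in a limited form. For participants with both periods, the baseline main effect drops out of the treatment estimate exactly, by algebra that needs no assumed values. The credit given to it in Section 3 is unsupported. The consequence is a misdescribed adjustment and possibly lost precision.

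How much precision is lost depends on how well baseline QtG predicts d1 − d2, which the document does not say. Some association is plausible: t0 is subtracted in d1 but not in d2, and entry below 25 on a 30-point scale leaves some participants little room to improve in the second block. Under the assumed range, power moves from about 81% to between 79% and 91%.

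A reader might conclude that baseline, stratum and days since injury should all interact with PERIOD in the primary model. The figures do not support that. With five covariates (four strata assumed, plus two continuous covariates), power at 34 participants is roughly 73–77% if they explain nothing, depending on how far stratification balances them. At R² = 0.1 it is only about 78–82%, so there is little or no gain. In the complete-pair simulation, adding stratum × PERIOD raised the empirical SD from 1.070 to 1.124.

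**What to change.** 1. In Section 2.7, add baseline QtG × PERIOD to the pre-specified primary model. For complete pairs this is the same as regressing d1 − d2 on sequence and baseline.
2. In Section 3, credit PERIOD with removing the average recovery difference between blocks, and baseline × PERIOD with baseline-dependent recovery. If the interaction is not adopted, credit PERIOD alone.
3. Keep stratum × PERIOD and days since injury × PERIOD as sensitivity analyses at most.

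The change affects wording and the analysis only, and uses data already collected at t0. It costs about 1 degree of freedom, or one to two points of power if baseline turns out not to predict d1 − d2. Data collection is expected to run until June 2028, so the change can be recorded well before analysis.

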## Abstract

Robot-assisted therapy (RT) is increasingly implemented in rehabilitation, yet evidence on its effectiveness in improving upper extremity function after cervical spinal cord injury (cSCI) remains limited. Therefore, this randomised crossover study aims to investigate the effects of unilateral RT compared to conventional unilateral occupational therapy (OT) on upper extremity function in individuals with cSCI. 40 participants with traumatic or non-traumatic cSCI (16–81 days post-injury, neurological level of injury: C1–T1) will be randomised (1:1), stratified by their predicted recovery profile, to receive 6 weeks of RT (ArmeoSpring) and 6 weeks of OT in random order, each 3 × 30 min/week in addition to the clinical routine therapy. Assessments are conducted before (t_0_), between (t_1_) and after both intervention blocks (t_2_ and t_3_). The primary outcome is the Quantitative Grasping Subtest of the Graded Redefined Assessment of Strength, Sensibility, and Prehension (GRASSP-QtG); primary analysis uses a linear mixed model to estimate the treatment effect based on change scores. Recruitment is currently ongoing. This randomised crossover study allows the collection of a comprehensive dataset to generate knowledge about treatment effectiveness, enabling future individuals with cSCI to benefit from improved and individualised therapy schedules.

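### The primary model's random intercepts cannot represent a negative correlation between two consecutive changes that share t1, so the 5% test may be anti-conservative if that correlation is negative

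*Protocol article*

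**What the plan says.** The Abstract says that the "primary analysis uses a linear mixed model to estimate the treatment effect based on change scores". Section 2.7 repeats this: "The primary and secondary outcomes will be analysed as changes within each period using linear mixed models". It names the two responses per participant as t1 minus t0 and t2 minus t1. The fixed effects are the study baseline, TREATMENT and PERIOD.

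For the dependence between a participant's two responses, the section relies on one device: "subject- and stratum-specific random intercepts will account for within-subject and within-stratum correlation across timepoints". It states no residual covariance structure. A second model, used to examine carryover, adds SEQUENCE and the TREATMENT by PERIOD interaction.

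On inference it states: "A two-sided significance level of α = 0.05 will be used for superiority testing". R is named as the software, but no package and no degrees-of-freedom method.

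**The concern.** A random intercept suits repeated measurements that share something with the same sign, such as a person's general level. Consecutive changes also share something with opposite signs, the t1 score. If a participant happens to perform well at t1, the first change goes up and the second goes down by the same amount.

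Three forces push the correlation down: visit error at t1, the 30-point maximum of the scale (Table A1), and recovery that slows over time. One force pushes it up: some participants recover faster than others in both blocks.

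If the net result is negative, the estimated subject variance falls to zero, the fit is singular, and the model treats the two changes as independent. It then loses the pairing that the crossover is meant to exploit. The primary test rejects too often and its confidence interval is too narrow. The interval matters as much as the test, because section 2.7 presents estimation as the main aim.

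**Working it through.** **1. The plan's own figure.** Section 2.7 says that "a sample size of 34 evaluable participants will allow detection of a minimal clinically important difference (MCID) of three points", "as long as the corresponding within-group standard deviation does not exceed six points", at 80% power and two-sided 5%. As a paired t-test with d = 3/6 = 0.5, n = 33 gives power 0.795 and n = 34 gives 0.808. With "accounting for a 15% attrition rate", 34/0.85 = 40. Both figures reproduce if 6 points is the SD of the paired difference. The calculation therefore relies on a within-participant error term.

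**2. Covariance of the two changes.** Let visit errors be independent with variance s², and let nothing else vary.
- Var(t1 - t0) = Var(t2 - t1) = 2s²
- Cov(t1 - t0, t2 - t1) = -s²
- rho = -s²/(2s²) = -0.5

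A random intercept adds a covariance equal to its own variance, which is zero or more.

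**3. Effect on the standard error.** For changes with common variance v, the within-participant contrast has variance 2v(1 - rho). On the zero boundary the model uses 2v. So true SE / model SE = sqrt(1 - rho), and actual size = 2[1 - Phi(1.96/sqrt(1 - rho))]. Interval coverage is one minus the size.

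| rho | true SE / model SE | actual size |
|---|---|---|
| 0 | 1.000 | 5.0% |
| -0.1 | 1.049 | 6.2% |
| -0.25 | 1.118 | 8.0% |
| -0.5 | 1.225 | 10.95% |
| -0.75 | 1.323 | 13.8% |

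The article gives no value for rho; the range is an assumption.

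**4. Simulation check** (n = 34, balanced sequences, baseline covariate, REML with the subject variance bounded at zero, 20,000 trials per scenario).

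| Scenario | rho | random intercept | within-participant contrast |
|---|---|---|---|
| visit error only | -0.5 | 10.8% | 4.8% |
| plus independent block-to-block variation | -0.33 | 9.2% | 5.0% |
| the same, with more of that variation | -0.16 | 7.0% | 5.0% |
| recovery-rate differences offset the error | 0 | 5.6% | 4.9% |
| recovery-rate differences dominate | +0.5 | 5.2% | 5.2% |

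In the first scenario the subject variance sat on the boundary in 99.9% of trials. In a smaller run of that scenario with a stratum intercept also fitted (1,500 trials), the size was about 9.5% to 10.6%, so the stratum term does not repair it.

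**5. Ceiling and slowing recovery.** Assumptions: visit-error SD 2, baseline uniform from 4 to 24, mean gain 4 in block 1 and half of each person's gain again in block 2, scores rounded and capped at 30. With person-specific gain SD of 0, 1, 2 and 3 points, the random-intercept test ran at about 11%, 10% to 11%, 8% and 6%. With gain SD 3 but no cap and no slowing it ran at 4.9%.

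**The case against.** The strongest reply is that 11% needs an extreme assumption. It requires that participants do not differ in true recovery, whereas the trial enrols AIS A to D, levels C1 to T1, from day 16 to day 81 (Table 1), and stratifies by predicted recovery profile because recovery differs (section 2.2).

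The plan's SD of 6 also limits the size. Treat the remaining variation as independent across blocks, with visit-error SD e as an assumption.
- If 6 is the SD of the paired difference, each change has variance 18 - e² and rho = -e²/(18 - e²). Then e = 1, 1.5 and 2 give 5.7%, 6.7% and 8.4%. Reaching 11% needs e = 2.45, a smallest detectable change of 1.96 x sqrt(2) x 2.45 = 6.8 points.
- If 6 is the SD of each change, rho = -e²/36. Then e = 1, 2 and 3 give 5.3%, 6.3% and 8.0%. Reaching 11% needs e = 4.24, a detectable change of about 11.8 points.

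Either is more than twice the 3-point difference sought. This stands: modest visit error alone implies modest inflation, and persistent differences in recovery rate lower it further. In the other direction, the ceiling and slowing recovery can offset those differences, as step 5 shows. Adjusting for baseline and stratum may also absorb part of the positive component.

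Two further replies stand in part. The zero bound is a property of the usual R mixed-model fit, and no package is named; an unbounded compound-symmetry fit would avoid the problem. The trial is also described as primarily exploratory, which lowers the stakes, but section 2.7 keeps a formal superiority test at 5%.

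**Conclusion.** The structural point holds. Section 2.7 names the two responses and the mechanism meant to handle their correlation, and that mechanism cannot represent a negative one. This is therefore not a detail left to an unseen analysis plan. The consequence is conditional: about 6% at rho = -0.1, 8% at -0.25 and 11% at -0.5, with little or no inflation at rho of zero or above. These figures assume a zero-bounded fit and a correlation that the article does not give. This should be fixed, with moderate confidence in the size of the inflation.

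A reader might infer more than the document supports:
- **That the primary test will run at 11%.** That is the case of visit error alone, not a forecast. It is not a strict ceiling either, since rho below -0.5 would give more.
- **That the correlation must be negative.** The forces oppose each other, and the article has no reliability or correlation figure with which to settle the sign.
- **That the sample size is wrong.** As a paired calculation, 34 and 40 reproduce; the model's covariance is what does not match it.

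**What to change.** In section 2.7, replace the subject random intercept with a within-participant covariance that is free to be negative. Either of these would do:
- an unstructured 2x2 residual covariance for the two changes (gls or mmrm in R), with Kenward-Roger or Satterthwaite degrees of freedom where the package provides them; or
- a joint model of the t0, t1 and t2 scores with an unstructured covariance.

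Name the package and the degrees-of-freedom method in the same sentence.

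The cost is one extra covariance parameter and the small-sample degrees of freedom that go with it. No data, visits or participants are affected. Data collection is expected to run until June 2028, so the change can be prespecified.

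The new analysis should not be described as simply a two-sample t-test of the difference between the two changes, nor as always giving the random-intercept SE when rho is positive. Both need equal variances of the two changes; a SEQUENCE term also gives the t-test equivalence, but the primary model has none. For example, with change SDs of 8 and 4, rho = 0.3, 17 per sequence and known covariance:
- t-test: sqrt[(1/4) x (64 + 16 - 19.2) x (2/17)] = 1.34
- generalised least squares: 1/sqrt[34 x (1/4) x 99.2/931.84] = 1.05
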